## Abstract

**Background:**

Transthyretin amyloid cardiomyopathy (ATTR-CM) is a systemic amyloidosis disorder with early clinical manifestations similar to other heart conditions, which complicates its diagnosis and management. The disease’s insidious nature and its progression to heart failure emphasize the critical need for enhanced recognition and understanding of its clinical landscape.

**Objective:**

This study aimed to understand the natural history and current treatment patterns for managing ATTR-CM in a diverse Asian cohort from Taiwan, Hong Kong, and Malaysia.

**Methods:**

This study is a multicenter, noninterventional disease registry that plans to enroll patients diagnosed with ATTR-CM across approximately 17 sites in Taiwan, Hong Kong, and Malaysia. Almost 350 patients with a documented diagnosis of ATTR‑CM after June 1, 2019, will be enrolled in the study. Deceased patients will be enrolled without the need for consent in accordance with applicable regulations. Their data will be gathered retrospectively through a 1-time review of their medical records, where permissible. Data related to clinical characteristics, treatment, and outcomes will be collected for each patient during the routine clinical practice while adhering to local standards of care. The end of data collection is planned for at least 12 months after the end of the enrollment period.

**Results:**

As of March 16, 2025, ethical approvals for this study have been obtained or are under review at multiple sites across Taiwan, Hong Kong, and Malaysia. The study commenced on October 1, 2024, with the first participant’s first visit and so far, 59 patients have been recruited: 35 from National Taiwan University Hospital (Taiwan), 13 from Taipei Veterans General Hospital (Taiwan), 2 from China Medical University Hospital (Taiwan), 2 from Sarawak Heart Center (Malaysia), and 7 from Queen Mary Hospital (Hong Kong). An interim report is scheduled for completion by December 31, 2025. The end of data collection, marked by the last participant’s visit, is planned for October 1, 2027, and the final study report is expected to be finalized by June 1, 2028. Once established, the database will serve as a comprehensive resource for analyzing baseline characteristics, treatment patterns, and outcomes in patients with ATTR-CM from diverse health care systems.

**Conclusions:**

This research will aid in understanding the demographic, clinical, and therapeutic patterns of ATTR-CM in Taiwan, Hong Kong, and Malaysia. This registry may influence advancements in early detection, diagnosis, and tailored treatment strategies in ATTR-CM.

**Trial Registration:**

ClinicalTrials.gov NCT06651073; https://clinicaltrials.gov/study/NCT06651073

**International Registered Report Identifier (IRRID):**

DERR1-10.2196/71314

## Introduction

### Background

Transthyretin amyloid cardiomyopathy (ATTR-CM) is a systemic amyloidosis disorder caused by the accumulation of misfolded transthyretin proteins, leading to the formation of amyloid fibrils in the extracellular space [1]. These fibrils alter tissue structures and impair the function of various organs [1]. Due to nonspecific symptoms, ATTR-CM diagnosis is often delayed or missed [2]. If untreated, ATTR-CM is a fatal disorder, commonly progressing to congestive heart failure (HF), cardiac arrhythmia, conduction system disease, and complete HF [2,3]. Despite its severity, there is a scarcity of research, especially in Asia, on disease progression, treatment practice, clinical outcomes, and disease mortality in ATTR-CM [4].

ATTR‑CM can be classified by the sequence of the *ATTR* gene, either wild-type, with no mutations (wt*ATTR*), or hereditary, with a mutation (h*ATTR*) [5]. Disease progression is generally slower in wt*ATTR*, whereas h*ATTR* often progresses more rapidly due to increased amyloid accumulation [5]. Many different mutations have been found in the *ATTR* gene, leading to variability in the initial signs and symptoms among patients with h*ATTR* depending on their specific genetic mutations [6,7]. In people of Chinese descent in Taiwan and Malaysia, Ala97Ser is found to be the most prevalent genotype, where it accounts for more than 90% of *ATTR* gene variations among affected individuals [8,9].

As ATTR-CM is an underrecognized disease, reported global prevalence rates vary, and the true prevalence remains uncertain [10,11]. A previous study suggested a prevalence rate of approximately 13% in patients with HF and myocardial wall thickening of more than 12 mm [12]. However, there are no large-scale studies, and the actual prevalence of ATTR-CM in Asia remains unclear [4].

Understanding the demographic and clinical characteristics of patients with ATTR-CM across a variety of health care systems is crucial for enhancing the recognition and early detection of the disease [13].

A panel of experts from Europe and the United States recommended three key approaches for monitoring the progression of ATTR-CM: (1) clinical and functional endpoints, (2) biomarkers and laboratory markers, and (3) imaging and electrocardiograph parameters (Figure 1) [2,4]. However, across Asian populations, the pathological presentation of ATTR differs, and expert consensus on monitoring the progression of ATTR-CM will vary across regions [14-16]. Due to limitations in health care accessibility across Asia and variations in clinical practice, there are alternative recommendations that take perspectives from Asian countries into consideration (Figure 1) [2,4].

**Figure 1 figure1:**
[figure not shown]
Criteria for assessing disease progression in patients with ATTR-CM. Consensus from experts recommends the three domains above for the long-term monitoring of patients with ATTR-CM. 6MWT: 6-minute walk test; ATTR-CM: transthyretin amyloid cardiomyopathy; ECG: electrocardiography; HF: heart failure; KCCQ: Kansas City Cardiomyopathy Questionnaire; LV: left ventricle; NAC: National Amyloidosis Centre (United Kingdom); NT-proBNP: N-terminal pro-B-type natriuretic peptide; NYHA: New York Heart Association.

In assessing clinical and functional endpoints, the 6‐minute walk test remains a widely accessible and cost-effective tool in Asia [17]. In addition, measuring cardiac biomarkers, such as serum N‐terminal pro-brain natriuretic peptide and serum cardiac high‐sensitivity troponin, is useful for measuring disease progression [18,19]. However, in the event of poor accessibility, alternatives in imaging and electrocardiogram tools have not yet been established [4]. Clinical experience in Asia suggests, for example, that a “relative” low electrocardiogram voltage as an alternative to left ventricle wall thickness would be an important indicator of ATTR-CM progression in Asian patients [4]. Echocardiography is also suggested, as it is generally available across Asia. Clearly, there is a need for research that augments the methods and tools used to diagnose and monitor ATTR-CM progression. Monitoring these disease domains through a registry would aid in understanding the characteristics and progression of ATTR-CM in Taiwan, Hong Kong, and Malaysia, ultimately, this is needed to improve disease recognition, detection, and appropriate management across these regions [20].

Singapore and Thailand have established country-level patient registries for ATTR-CM; however, there is a pressing need for other Asian countries to develop similar registries as well as compare the data across countries in the Asian region [4,21]. In this article, we describe the protocol for a multicenter, noninterventional disease registry to characterize the natural history of ATTR-CM and treatment patterns in patients clinically diagnosed with ATTR-CM across Taiwan, Hong Kong, and Malaysia. This dataset, spanning 3 diverse nations, is essential for building a robust population base that captures variations in ethnicity, socioeconomic status, and medical insurance coverage, while also reflecting differences in clinical care practices across varied health care systems [13].

### Aims and Objectives

This study aims to understand the natural history and treatment patterns of patients with ATTR-CM in Taiwan, Hong Kong, and Malaysia. Primary, secondary, and exploratory objectives, respectively, are listed in Textbox 1.

Study objectives.To characterize the natural history of patients with transthyretin amyloid cardiomyopathy (ATTR-CM), described by patient demographic and clinical characteristics at diagnosis of patients with ATTR-CM, and patient outcomes.To describe the treatment patterns in patients with ATTR-CM and to identify the prognostic factors for all-cause mortality and cardiovascular-related hospitalization in patients with ATTR-CM.To assess treatment effectiveness in patients with ATTR-CM and to evaluate the quality of life and health care resource usage in patients with ATTR-CM.

## Methods

### Study Design and Setting

This multicenter, noninterventional, disease registry enrolling approximately 350 patients diagnosed with ATTR-CM will be conducted across approximately 17 sites in Taiwan, Hong Kong, and Malaysia. All patients with a documented diagnosis of ATTR‑CM after June 1, 2019 will be invited to participate in the study. The study size will be based on the number of eligible ATTR-CM cases identified in the medical records and meeting the inclusion criteria. However, the goal is to enroll approximately 350 patients diagnosed with ATTR-CM across the sites, with data collected throughout routine clinical practice. As it is a noninterventional study, no procedures or treatments will be mandated, and patients will receive their usual clinical care. The observation period for each patient will range from the index date (ie, the date of first documented ATTR-CM diagnosis) to whichever occurs first of death, patient withdrawal of consent, loss to follow-up, or end of data collection. The end of data collection is planned for a minimum of 12 months after the end of the enrolment period. This will allow all patients to have the opportunity to contribute at least 12 months of follow-up data (Figure 2).

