**Figure 2 figure2:**
[figure not shown]
Study design. ATTR-CM: transthyretin amyloid cardiomyopathy; ICF: informed consent form. The “index date” marks the point of first diagnosis, which may coincide with or precede study enrollment. Patients are then followed over time, capturing both retrospective data (before the index date) and prospective data (after the index date), at approximately 3-month intervals. The “observation period” extends from the index date until either the end of the study, patient death, withdrawal of consent, or loss to follow-up. Data are collected through a combination of retrospective review during a one-time medical record abstraction and routine clinical visits for prospective information.

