#### Study Participants

The inclusion criteria of this ATTR-CM registry are as follows: (1) adults (aged ≥18 years) at first ATTR-CM diagnosis; (2) confirmed diagnosis of ATTR-CM after June 1, 2019; and (3) able to provide informed consent. The eligibility criteria are broad enough to include all patients with ATTR-CM without any exclusion criteria.

Several strategies to address potential selection bias will be implemented. Each eligible patient will be consecutively assessed during the designated period using predefined criteria to ensure comprehensive inclusion and reduce bias. Recruitment will span a variety of clinical settings to capture a diverse and representative sample. The eligibility criteria are designed to be broad, promoting inclusivity and enhancing the generalizability of our findings. In addition, a screening log for individuals who do not participate will be maintained to gather minimal deidentified information to identify any systematic differences and further understand potential biases. Each enrolled participant or his or her legally acceptable representative will be provided with an informed consent form (ICF) that outlines the study objectives, procedures, risks, and benefits, and clearly states that participation is voluntary with the option to opt out at any time without affecting their clinical care.

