### Data Analysis

Detailed methodology for summary and statistical analyses of data collected in this study is documented in a statistical analysis plan. This study is descriptive and does not involve hypothesis testing, hence the actual sample size will be determined by the number of eligible ATTR-CM cases identified in the medical records that meet the inclusion criteria. Approximately 350 patients diagnosed with ATTR-CM are expected to be enrolled based on feasibility assessments, historical diagnosis rates, and the expected patient volume at the 17 participating sites across Taiwan, Hong Kong, and Malaysia. Continuous variables will be summarized using descriptive statistics, including the number of participants with nonmissing and missing values, mean, SD, median, 25th percentile (Q1), 75th percentile (Q3), minimum, maximum, and median (IQR). Means and medians will be presented with one more decimal place than the raw data, while SDs will be presented with 2 more decimal places. Categorical variables will be summarized using frequency counts (n) and percentages (%), with percentages calculated over nonmissing data.

Time-to-event analysis will be performed using the Kaplan-Meier methodology. Data will be presented as the number of patients at risk, with the event, and censored. The estimated median, Q1, Q3, and the 2-sided 95% CI, using Brookmeyer and Crowley method, will be provided for the main statistical estimators. CIs about a parameter estimate will be presented using the same number of decimal places as the parameter estimate.

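### Survival is counted from a diagnosis that may precede enrolment by more than 5 years, and entry depends on vital status, so a Kaplan-Meier curve from diagnosis can be biased in either direction

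*Protocol article*

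**What the plan says.** **Time origin.** Study Design and Setting: "The observation period for each patient will range from the index date", defined as the first documented diagnosis, up to death, withdrawal, loss to follow-up or end of data collection. The Figure 2 legend says that the index date is one "which may coincide with or precede study enrollment".

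**Dates.** Diagnosis must fall after June 1, 2019 (Study Participants). On enrolment, the abstract says "The study commenced on October 1, 2024", and the end of data collection "is planned for October 1, 2027", at least 12 months after enrolment closes.

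**Route of entry.** The inclusion criteria end with "after June 1, 2019; and (3) able to provide informed consent". The abstract adds: "Deceased patients will be enrolled without the need for consent in accordance with applicable regulations", with a single record review where this is allowed. Ethical Considerations lists the consent waiver for the deceased among the documents with prospective ethics approval, without saying which sites it covers.

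**Analysis.** Data Analysis says that time-to-event "analysis will be performed using the Kaplan-Meier methodology", and refers detail to a statistical analysis plan that is not shown. The stated protections against selection bias are consecutive assessment, broad criteria and that "a screening log for individuals who do not participate will be maintained".

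**The concern.** A patient who is enrolled alive cannot have died between diagnosis and consent. A death in that interval would have moved the patient to the other route of entry. If the interval is counted as time at risk, the curve is right only when those who died in it are sampled at the same rate as those who survived it. Here the two routes have different gatekeepers: personal consent for the living, regulatory permission and record access for the dead. Nothing in the article makes the two rates equal, and none of its safeguards changes who is in the risk set. The Discussion concedes selection bias only from the choice of centres.

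Patient outcomes belong to the primary objective, and prognostic factors for all-cause mortality and cardiovascular hospitalisation to the secondary one. An interim report is due by December 31, 2025, while enrolment is under way.

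The sampling rule is also unclear on its face. The inclusion criterion on ability to consent makes no exception for the deceased patients whom the abstract enrols.

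**Working it through.** The article has no survival estimate, power or precision figure to reproduce; the 350 patients are a feasibility target.

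**1. Dates (from the article)**
- June 1, 2019 to October 1, 2024: 1,949 days / 365.25 = 5.34 years.
- Enrolment must close by about October 1, 2026 (12 months before October 1, 2027). The longest possible gap from diagnosis to enrolment is then 2,679 / 365.25 = 7.33 years.

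**2. Mechanism for one gap**

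Let S be true survival, g the gap from diagnosis to enrolment, p_d the probability of capturing a patient who died before g, and p_a that of enrolling one alive at g. Among those sampled, survival at t ≥ g is

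S*(t) = p_a S(t) / [p_d (1 − S(g)) + p_a S(g)].

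If p_d = p_a, then S*(t) = S(t), so equal capture gives no bias. Take g = t = 3 years and S(3) = 0.50:
- p_d = 0: 0.50 / 0.50 = 100%.
- p_d = 0.5, p_a = 1: 0.50 / (0.25 + 0.50) = 67%.
- p_d = 1, p_a = 0.8: 0.40 / (0.50 + 0.40) = 44%.
- p_d = 1, p_a = 0.6: 0.30 / (0.50 + 0.30) = 38%.

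Patients enrolled at diagnosis (g = 0) are not affected, so the whole-cohort effect is smaller.

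**3. Whole cohort, by simulation**

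Assumptions, none of them from the article: exponential survival; diagnoses uniform from June 2019 to October 2026; patients diagnosed before October 2024 approached uniformly from October 2024 to October 2026, later ones enrolled at diagnosis; follow-up to October 2027; capture depends only on vital status at enrolment. With a true median of 3 years, about 40% of eligible patients die before enrolment.

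| Pre-enrolment deaths captured | Living patients consenting | 3-year survival, Kaplan-Meier from diagnosis (truth 50%) |
|---|---|---|
| none | all | 74% |
| half | all | 59% |
| 80% | 80% | 50% |
| all | all | 50% |
| all | 80% | 47% |
| all | 60% | 43% |

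Delayed entry (patients enrolled alive, at risk only from enrolment) returns 50% in every row.

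Other medians show the same pattern. At a true median of 3.5 years (true 3-year survival 55%), the curve reads 78% with no deaths captured, 61% with half the deaths and 80% consent, and 52% with all deaths and 80% consent. At a median of 5 years (true 66%), it reads 85%, 72% and 63%.

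**4. Scale against sampling error**

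The 95% half-width for a proportion of 50% at n = 350 is 1.96 × √(0.25/350) = 5.2 points. The error with no deaths captured (+24) or half captured (+9) exceeds this. The error with all deaths and 80% consent (−3) does not.

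**5. Price of delayed entry at n = 350**

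Root-mean-square error of 3-year survival, true median 3 years, in points:
- All deaths, 90% consent: about 3 from diagnosis, about 5 with delayed entry.
- All deaths, 80% consent: about 4 against 5.
- All deaths, 60% consent: about 8 against 5.

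**The case against.** The strongest reply is that the naive curve is inferred. The article names Kaplan-Meier but gives no rule for entry to the risk set, and a left-truncated Kaplan-Meier is still Kaplan-Meier. Such a rule usually sits in the analysis plan, so its absence from an article is no error. This stands, and it is why the point is worded as what can happen. The time origin, the two routes of entry and the unreconciled consent criterion are nevertheless stated in the article itself.

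The design also goes some way to meet the problem. It enrols the deceased, lists an approved waiver, invites all eligible patients, assesses them consecutively, allows consent by a representative and logs non-participants. With equal capture there is no bias. This stands too, but a waiver that applies everywhere does not settle the matter: if all deaths enter and some living patients decline, the bias reverses.

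A reader might infer more: that the curves are biased, that the direction differs by site because waivers differ by site, and that apparent differences between Taiwan, Hong Kong and Malaysia could follow from consent rules alone. The documents do not support this. No site is shown to lack a waiver, several sites share one approval, and Data Analysis states no survival comparison between countries. The limit on access to deceased patients' records shows only that variation is possible.

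Finally, delayed entry is not always the better estimator. With good capture at n = 350 it has the larger error, and it discards every death before enrolment. That argues against making it the sole main analysis.

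**Conclusion.** The concern holds as a risk of bias in either direction, not as a demonstrated bias. Diagnosis as the time origin, a gap that can exceed 5 years and entry that depends on vital status are all fixed by the article. Followed literally, with all time since diagnosis at risk, they give unbiased survival only if deceased and living patients are captured about equally.

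Under the assumptions above (true median 3 years), the error in 3-year survival runs from +24 points with no deaths captured, through zero with equal capture, to −3 points at 80% consent and −7 at 60% consent with all deaths captured. The outer figures are extremes, not expectations: the first contradicts the plan to enrol deceased patients, and the 60% consent rate is hypothetical. Actual capture rates are not in the documents, and the analysis plan may already handle delayed entry.

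The simulation also lets willingness to enrol depend only on vital status. If frailer living patients decline more often, delayed entry would not remove that bias.

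**What to change.** 1. **Reconcile the entry rule.** Bring the inclusion criterion on ability to consent into line with the enrolment of deceased patients, and state where the waiver applies.
2. **Report capture.** Tabulate, by site and country, the eligible living and deceased patients identified and enrolled. The screening log should record vital status for this. The count is hard to rebuild later, so it should start now.
3. **Add a delayed-entry analysis.** In Data Analysis, report beside each curve from diagnosis a left-truncated Kaplan-Meier on the same time scale, with patients enrolled alive at risk only from enrolment. Use (entry, exit] risk sets in any Cox model. For first cardiovascular hospitalisation, say how events between diagnosis and enrolment are handled.
4. **State how to read the pair.** Treat the curve from diagnosis as unbiased only where capture of both groups is complete or similar.

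**Cost.** Wording in the protocol and analysis plan, one more field in the log if vital status is not already there, and one more curve per outcome. The delayed-entry curve leaves out deaths before enrolment and is less precise (about 5 against 3 points of error in 3-year survival at n = 350 with good capture). It should therefore accompany the full-cohort curve and not automatically replace it.

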Multimedia Appendix 1 provides further details on each data collection element, including the timepoints at which the data will be recorded. The study case report form (CRF) includes an “ATTR-CM diagnosis” section detailing the methods used to diagnose ATTR-CM. The CRF captures a range of clinically validated approaches, including functional classification, imaging, biomarker screening, and genetic testing, consistent with established guidelines for ATTR-CM diagnosis.

The collected data will be from reliable sources of patient-level information available at the participating sites. This includes data available in the patients’ electronic medical records as well as medical charts and any other documentation or communication by health care providers. All data listed above will be collected by trained site personnel and entered directly into the web-based electronic case report forms (eCRFs) at each participating study site. Sites will be responsible for entering extracted patient data into a secure Electronic Data Capture (EDC) database and all changes or corrections to eCRFs will be documented in an audit trail. The personal data will be stored at the study site in encrypted electronic or paper form and will be password-protected or secured in a locked room to ensure that only authorized study staff have access. Patient data will be deidentified before analysis. All identifiable information will be replaced with a unique patient-specific identifier, and data will be transmitted and managed using encryption.

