## Results

The study began on October 1, 2024, with the first participant’s visit, and as of March 16, 2025, a total of 59 patients have been recruited. These include 35 patients enrolled from National Taiwan University Hospital, 13 patients recruited from Taipei Veterans General Hospital, and 2 patients enrolled from China Medical University Hospital in Taiwan. Two patients have been recruited from Sarawak Heart Center in Malaysia, and 7 patients enrolled from Queen Mary Hospital in Hong Kong. We anticipate that data collection will continue robustly, with an interim report scheduled for completion by December 31, 2025. The final phase of data collection, marked by the last participant’s visit, is planned for October 1, 2027, and the final study report is expected to be finalized by June 1, 2028. Once established, the resulting database will serve as a valuable resource for analyzing baseline characteristics, treatment patterns, and outcomes in patients with ATTR-CM. This extensive dataset will not only provide insights into current clinical management but also guide future research efforts and inform evidence-based clinical practices in managing ATTR-CM.

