Establishing registries for rare diseases like ATTR-CM is fundamental to enhancing patient care pathways and ultimately improving disease outcomes [30,31]. Such registries are instrumental in generating RWE; they offer a systematic approach to monitor disease progression and assess the efficacy and safety of various treatment modalities [32]. The data compiled as per this protocol will enable a comprehensive understanding of ATTR-CM in the Asian context. An ATTR-CM registry for Asian countries is a critical step toward evaluating health care burden, clinical progression, health care strategies, and potential disparities. It will also facilitate a deeper analysis of treatment efficacy and safety, thereby improving the overall standard of care for patients with ATTR-CM [4].

As a multicenter, noninterventional, disease registry study aiming to collect real-world data on ATTR-CM, there are multiple strengths with this study design. Given the frequent undiagnosed instances of ATTR-CM in various clinical settings, this protocol is designed to ensure that the study sample accurately represents the target population through systematic patient assessment, nonrestrictive recruitment, and inclusive inclusion criteria. However, there are also some potential limitations inherent to the design of any multicountry and multicentric study. Center selection was based on each center’s readiness to participate and the availability of patients diagnosed with ATTR-CM. Consequently, while the protocol uses systematic patient assessment with broad, inclusive criteria, the study sample may not fully capture the national or regional prevalence or diagnosis rates of ATTR-CM. This targeted recruitment approach may introduce selection bias, potentially limiting the generalizability of the findings. Furthermore, variations in routine clinical care and adherence to standard practice guidelines across these multiple sites in different countries may affect the consistency, completeness, and types of data collected.

Despite these limitations, this study aims to make substantial contributions to the limited existing literature on ATTR-CM by documenting the natural history and treatment patterns of patients in Taiwan, Hong Kong, and Malaysia. It holds the potential to improve the detection and management of ATTR-CM in Asia, ultimately improving patient outcomes and increasing survival rates.

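### Time at risk starts at first diagnosis, which need not be the enrolling site's, while data are limited to what that site holds, so admissions before referral may be under-captured

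*Protocol article*

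**What the plan says.** All references are to the Protocol article.

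- **Start of the clock.** Study Design and Setting: "The observation period for each patient will range from the index date (ie, the date of first documented ATTR-CM diagnosis". Observation ends at the earliest of death, withdrawal of consent, loss to follow-up and end of data collection. The Figure 2 legend says that the index date "marks the point of first diagnosis, which may coincide with or precede study enrollment".
- **Eligibility.** Study Participants asks for adult age at first diagnosis, a "confirmed diagnosis of ATTR-CM after June 1, 2019" and ability to consent. It does not say where the diagnosis must have been made.
- **Data source.** Data Collection and Management: "The collected data will be from reliable sources of patient-level information available at the participating sites". The sentence after it counts electronic records, charts and other providers' documentation or communication among these sources. Under the Figure 2 legend, past data come from a single record abstraction.
- **Outcomes concerned.** Admissions (with dates and reason) and emergency visits are collected. Cardiovascular hospitalization is named in the secondary objective and health care resource use in the exploratory one.
- **Analysis.** Data Analysis specifies Kaplan-Meier for time-to-event outcomes.

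**The concern.** The clock and the source of events are defined by different things: the clock by a diagnosis date, the events by what one site holds. They coincide for a patient diagnosed at the enrolling site. For a patient diagnosed elsewhere, the interval up to first site contact counts as observed, but an admission in it is seen only if some document about it reached the site. An unseen admission is treated as no admission.

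Three results are exposed:

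- Cardiovascular-hospitalization rates are biased downward, and time to first hospitalization upward. The gap lies at the start of follow-up, so early Kaplan-Meier estimates suffer most.
- Resource use, including emergency visits, is understated.
- If referral is commoner at some sites or in some countries, equal true rates look different. The Introduction gives comparison across countries as a reason for such registries.

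This is a matter of event capture in living and deceased patients alike, separate from who survives to be enrolled.

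**Working it through.** **No figure to reproduce.** The study is descriptive, and its target of about 350 patients rests on feasibility. The article gives no event rate, referral share, lag or capture rate. The dates can be checked; the rest is illustration.

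**Step 1: how long can diagnosis precede enrolment?**
- The earliest index date is just after June 1, 2019. On the start: "The study began on October 1, 2024, with the first participant’s visit". June 2019 to October 2024 is 5 years 4 months, about 5.3 years.
- On the end of data collection: "marked by the last participant’s visit, is planned for October 1, 2027". Also: "The end of data collection is planned for a minimum of 12 months after the end of the enrolment period". Enrolment can therefore run to October 1, 2026 at the latest, which makes the longest interval 7 years 4 months, about 7.3 years.

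These are upper limits. Only the part before first site contact is at issue.

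**Step 2: effect on a rate.** Let s be the share diagnosed elsewhere, g the months from diagnosis to first site contact, T the mean follow-up in months from diagnosis, and c the share of outside events that reach the site file. With a constant event rate:

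share of person-time in the gap = s × g / T

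shortfall in the observed rate = s × g × (1 − c) / T

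| s | g | T | c = 0 | c = 0.5 |
|---|---|---|---|---|
| 20% | 6 | 48 | 0.20 × 6 / 48 = 2.5% | 1.25% |
| 40% | 12 | 36 | 0.40 × 12 / 36 = 13.3% | 6.7% |
| 40% | 12 | 24 | 0.40 × 12 / 24 = 20% | 10% |

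All four inputs are assumptions, and the range is not a bound: s = 10%, g = 3, T = 36 gives 0.8% at c = 0, and s = 50%, g = 12, T = 24 gives 25%. If admissions cluster around diagnosis, the shortfall is larger than the formula gives.

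**Step 3: effect on 12-month cumulative incidence of first hospitalization.** Assume a constant rate h = 0.5 per year, c = 0, and L = g/12 of at most 1 year. A referred patient's first recorded admission can then fall only after site contact:

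observed = (1 − s)(1 − exp(−h)) + s(1 − exp(−h(1 − L)))

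The true value is 1 − exp(−0.5) = 39.3%.

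- s = 10%, L = 0.25: 0.9 × 0.393 + 0.1 × 0.313 = 38.5%
- s = 30%, L = 0.5: 0.7 × 0.393 + 0.3 × 0.221 = 34.2%
- s = 50%, L = 1: 0.5 × 0.393 + 0.5 × 0 = 19.7%

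**Step 4: effect on a comparison.** Take two countries with the same true rate, g = 12, T = 36 and c = 0, one with 40% and the other with 20% referred. The apparent rate ratio is (1 − 0.133) / (1 − 0.067) = 0.93, produced by referral alone.

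**The case against.** The best case against has five parts.

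- **Whose documentation sets the index date is not stated.** If it is the first diagnosis in the site's own record, much of the gap disappears. This is possible, but the Figure 2 legend calls the index date the point of first diagnosis, and no text ties it to the site.
- **Outside documents are in scope.** A reader might infer that events before referral are never captured. The text does not support that: referral letters and discharge summaries held at the site count as sources. What stands is that capture may be incomplete, because the article accepts what the site holds and states no step to obtain the rest.
- **Referral is an inference.** On site choice the article says only: "Center selection was based on each center’s readiness to participate and the availability of patients diagnosed with ATTR-CM". That makes referred-in patients plausible but gives neither share nor lag.
- **Two further consequences are tempting but unsupported.** One is that treatment begun elsewhere will appear to start late; actual treatment start dates are collected, so a start date in the medication history stays correct. The other is that cardiovascular hospitalization is a named primary outcome; the primary objective speaks only of patient outcomes in general.
- **The full protocol, data-collection appendix and statistical analysis plan are not shown** and may hold a rule on late entry or outside records. If they do, the point is settled by saying so. It is still more than an omission, because the article's own rules, followed as written, count the interval as observed.

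The Discussion concedes that completeness may vary, but attributes this to differences in care and guideline adherence, not to care received before referral.

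**Conclusion.** The point holds as a possible under-capture. The article starts time at risk at a diagnosis that need not be the enrolling site's, draws data from what that site holds, and states no rule to align the two. The bias in hospitalization and emergency-visit rates is downward. Its size ranges from negligible to material, and the documents cannot fix it: the 2.5% to 20% shortfall rests on assumed referral shares, gaps and follow-up, a constant event rate and no outside capture, and it halves if half of the outside events reach the site file. Baseline description at diagnosis is not affected by this mechanism. The change should be made, because a date of first site contact that was never collected cannot be recovered by any analysis rule.

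**What to change.** - **Collect**, unless the eCRF already does, the date of first contact for ATTR-CM at the enrolling site, and a yes/no flag for whether outside records cover the interval from diagnosis.
- **Keep diagnosis** as the index date for baseline description and as the time scale.
- **Use late entry** for hospitalization, emergency-visit and resource-use rates: every patient enters the risk set at first site contact, or at diagnosis if contact came earlier. Report this beside the analysis that starts at diagnosis.
- **Do not let the start of the clock depend on whether outside records were obtained.** Such records may be likelier to exist where there was an admission, which would bias rates upward. Use the flag descriptively or in a sensitivity analysis.
- **State the remaining limits.** For time to first hospitalization, earlier outside events may be unknown in late entrants. Admissions to other hospitals after first contact can also be missed; late entry does not cure that.
- **Reconcile the Figure 2 legend**, which labels data after the index date as prospective although the index date may precede enrolment.

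The cost is two eCRF items, one definition in the analysis, back-filling for patients already enrolled (59 as of March 16, 2025), and some lost early person-time in referred patients.
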